## **INVESTIGATOR REPORTING RESPONSIBILITIES TO THE SPONSOR**

### **Serious Adverse Events**

SAEs (whether or not they are also UPs) must be reported on the SAE/UP Report Form and sent to the RCHSPB Clinical Safety Office (CSO) by fax or e-mail attachment. All deaths and immediately life-threatening SAEs due to any cause that occur during the course of the study must be reported to RCHSPB Clinical Safety Office by the clinical site Investigator within 1 business day after the clinical site becomes aware of the event, and all other SAEs must be reported as soon as possible, but no later than 3 business days.

Serious adverse events will be reported to:

RCHSPB Clinical Safety Office  
[name]  
[name]  
  
[contact]  
[contact]  
E-mail: [[contact]](mailto:[contact])

In addition, the clinical site Investigator will notify LMIV by email, fax, or telephone within 1 working day of notification of an SAE occurrence. (Contact: [name], [[contact]](mailto:[contact]), [contact], [contact]) SAEs which occur in Mali will be also be reported to the Medical Monitor within 1 working day of notification of occurrence. (Contact: [name], email: [[contact]](mailto:[contact]), telephone [name] [contact] Cell: [name].)

The LMIV Investigator will provide copies of all SAE reports occurring during this trial to the Safety Contact at Coley Pharmaceutical Group, a Pfizer Company. These reports will include related as well as unrelated SAE reports. All SAE reports sent to Coley/Pfizer will be reported on MedWatch Form FDA 3500A and will include the Investigator's assessment of causality.

### **Unanticipated Problems**

Non-serious AEs that are UPS must also be reported on the SAE/UP Report Form and sent to the CSO by fax or e-mail attachment no later than 7 calendar days of site awareness of the event. The UPs that are not AEs will not be reported to the Sponsor CSO.

## **Pregnancy**

Pregnancy itself is not an AE. However, complications of pregnancies are AEs and may be SAEs. Pertinent obstetrical information for all pregnancies will be reported to the CSO via fax or email within 3 business days from site awareness of the pregnancy. Pregnancy outcome data (e.g., delivery outcome, spontaneous, or elective termination of the pregnancy) will be reported to the CSO within 3 business days of the site's awareness of the outcome.

In the event that a female participant should become pregnant and it is known that the participant has been exposed to CPG 7909, LMIV shall inform Coley Pharmaceutical Group, a Pfizer Company, of this pregnancy as soon as possible and in no event later than 15 calendar days after LMIV's initial receipt of the information.

For each pregnancy, LMIV will provide Coley with a completed current version of Coley's Pregnancy Notification Form and Pregnancy Notification Follow-Up Form. These forms are subject to minor changes and the current versions will be supplied by Coley as soon as LMIV informs Coley that a pregnancy has occurred. These forms will be completed by the clinical site Investigator and forwarded to LMIV. At the time a pregnancy is diagnosed, LMIV will submit a completed Pregnancy Notification Form to Coley as well as a Pregnancy Notification Follow-up Form at the time of pregnancy outcome. Reports of exposure during pregnancy will be entered into the Coley safety database and will be forwarded to Coley Pharmaceutical Group, a Pfizer Company, via the country office as noted in **Section 9.4.2**.

## **INVESTIGATOR REPORTING RESPONSIBILITIES TO THE NIAID IRB**

### **Expedited Reporting to the NIAID IRB**

Unanticipated problems that are either AEs or non-AEs and protocol violations will be reported within 7 calendar days of site awareness. Serious Adverse Events that are possibly, probably, or definitely related to the research will be reported to the NIAID IRB within 7 days of site awareness, regardless of expectedness. Investigators will report within 15 days on any other event or condition regardless of grade, which in their judgment represents an event reportable to the NIAID IRB.

### **Annual Reporting to the NIAID IRB**

The following items will be reported to the NIAID IRB in summary at the time of Continuing Review:

- All unanticipated problems (including AEs and non-AEs)
- Expected serious adverse events that are possibly, probably, or definitely related to the research
- Serious adverse events that are not related to the research
- All protocol deviations which in the opinion of the Investigator should be reported
- Any trends or events which in the opinion of the Investigator should be reported

## **INVESTIGATOR REPORTING RESPONSIBILITIES TO LOCAL IRB(S)**

Site Investigators must comply with the reporting requirements of their local IRB/Ethics Committees (i.e. WIRB and FMPOS) The Investigators are also responsible for submitting IND

Safety Reports and UP summaries that are received from the IND Sponsor to their local IRB/Ethics Committee.

### **SPONSOR'S REPORTING RESPONSIBILITIES**

In accordance with the FDA Code of Federal Regulations (21 CFR 312.32), the IND sponsor RCHSPB must report serious and unexpected suspected adverse reactions (SUSARS) to the FDA and all participating Investigators in the form of a written IND Safety Report. AEs that are also UPs will be summarized by the IND Sponsor and distributed to the Investigators. Deaths and life-threatening events with any possible relationship to a study intervention must be reported to the FDA by telephone or fax as soon as possible but within 7 calendar days of RCHSPB's awareness. This initial report must be followed by as complete a written report as possible within 8 additional calendar days. All other IND Safety Reports must be submitted to the FDA as soon as possible, but no later than 15 calendar days after RCHSPB is notified of the SAE.

SAEs that do not meet the requirements for expedited reporting and all documented adverse events will be reported to the FDA in the IND annual report.

The FDA also requires sponsors to submit a written Safety Report of all serious and unexpected adverse events to all participating investigators of a trial. All participating investigators at all sites will be notified of any unexpected SAEs occurring at other sites in an IND Safety Report from RCHSPB. RCHSPB will also notify investigators of any revisions to the protocol or to the consent, or study closure. The study investigators in this study have the responsibility of promptly reporting all SAEs so that RCHSPB can comply with these regulations.

In addition, the Safety Office of RCHSPB will forward to Coley copies of all IND Safety Reports, using the same format as used to notify the FDA. Safety reports to Coley will not contain identifying or confidential information. All SAEs and safety related information are to be in writing and may be transmitted by fax using the Pfizer Investigator-Initiated Research Reportable Event Fax Cover Sheet to:

For U.S. Sites:

Pfizer U.S. Clinical Trial Department  
[name]  
[name]  
[contact]  
[contact]

For Mali, West Africa:

[name]  
Pfizer Afrique de l'Ouest  
Bureau de Cote d'Ivoire  
[name]  
[name]  
[name]  
Email: [contact]

[contact]  
[contact]

## **HALTING RULES**

The Principal Investigator will closely monitor study data as they become available and will make determinations regarding the presence and grading of adverse events. Adverse events will be evaluated with regard to the known complications associated with administration of CPG 7909 and other vaccine components. If a dose of vaccine is considered unacceptably reactogenic (as described in the following criteria), the study will be halted. No new enrollments and no further vaccinations will be administered by the Investigators until reviewed by the SMC and study IND Sponsor. A report of SMC recommendations will be submitted to the IRB. The following criteria will be used to define unacceptable reactogenicity of the malaria vaccine:

1. One or more subjects experience an SAE as defined in **Section 9.2** of this protocol that is determined to be possibly, probably, or definitely related to the vaccine, **or**
2. One or more subjects experience a hypersensitivity reaction that is probably or definitely related to the vaccine, **or**
3. Any severe clinical illness occurs that is not explained by a diagnosis that is unrelated to vaccination, **or**
4. Two or more subjects in any dose cohort (low dose US, high dose US, or Mali) experience any Grade 2 or higher laboratory abnormality (see **Appendix D**), or Grade 3 systemic AE that is determined to be possibly, probably, or definitely related to the vaccine as defined in this protocol. This does not include Grade 2 neutropenia resolving within 7 days of vaccination, which is an expected laboratory abnormality with CPG 7909 and which has not been associated with clinically significant events.

The IRBs, the NIAID, the pharmaceutical supporter(s), the FDA, or other government agencies, may discontinue the study at any time. Subsequent review of serious, unexpected, and related adverse events by the Medical Monitor, SMC or IRB, the IND sponsor, the FDA, and other regulatory authorities may also result in suspension of further administration of vaccine at the clinical site. The FDA, other regulatory authorities, and the study sponsor(s) retain the authority to suspend additional enrollment and administration of vaccine for the entire study as applicable.

## **10. CLINICAL MONITORING**

### **SITE MONITORING PLAN**

To ensure that the rights, safety, and well-being of the human subjects enrolled on this trial and to validate the Investigator's adherence to the protocol, applicable government regulations, and ICH/GCP guidelines, RCHSPB will provide oversight and monitor the compliance of this trial. Monitors will visit the clinical site to monitor all aspects of the trial in accordance with appropriate regulations. The objectives of a monitoring visit will be:

1. to verify the prompt reporting of all data points, including SAEs
2. to check the availability of signed informed consent
3. to compare individual subject's records (CRFs, electronic data, CRIMSON pulls) to the

source documents (supporting data, laboratory specimen records, clinical notes)

4. to ensure protection of study subjects, compliance with the protocol, and accuracy and completeness of records

The monitors will also inspect the clinical site's regulatory files to ensure that applicable regulatory requirements (FDA, OHRP) and guidelines (ICH) are being obeyed. During the monitoring visits, the Principal Investigator and/or designated study staff will be available to discuss the study. The site Principal Investigator will provide direct access and allow the study monitors, LMIV, and regulatory authorities in Mali and US to access all study-related documents.

Prior to the start of the study, the Principal Investigators will be informed of the frequency of the monitoring visits and will be given reasonable notification prior to each visit.

Quality control procedures will be implemented beginning with the data entry system, and data quality control checks that will be run on the database will be generated. Any missing data or data anomalies will be communicated to the site for clarification/resolution.

## **SAFETY MONITORING PLAN**

### **10.1.1 Safety Monitoring Committee (SMC)**

The LMIV, in consultation with the clinical trial sites and RCHSPB, will select 3 independent candidates to serve as monitors to advise RCHSPB and the study investigators on the trial. These individuals will be independent of LMIV and the clinical trial sites. RCHSPB will evaluate the candidates and coordinate the functions of the SMC. The SMC's primary responsibility will be to monitor subject safety. The Principal Investigator is responsible for ensuring that the SMC is aware of all new safety information. The SMC will meet to review the protocol prior to study initiation, and will review cumulative safety data up to at least 1 week after the first two vaccinations are complete in the US, and will give approval to proceed prior to enrollment and vaccinations in Mali. The SMC will also meet if stopping criteria are met, or as needed at the discretion of the SMC and/or study investigators. At any scheduled or unscheduled meeting, the SMC will review cumulative safety data for evidence of study-related AEs, adherence to the protocol, and factors that may affect outcome or study data such as protocol violations and losses to follow-up. One member of the SMC will be a Malian who is independent of the MRTC. Summaries of all SMC meetings will be sent to the FDA after review and approval by the SMC chair.

### **10.1.2 Medical Monitor**

An independent medical monitor, [name], has been appointed for oversight of safety in this trial in Mali. The medical monitor will be available to advise the Investigators on study-related medical questions or problems, and to act as a representative for the subjects' welfare. Additionally, the medical monitor may ask to convene a safety monitoring committee meeting for review of any safety issue or adverse event. Should the study be halted after vaccinations have begun in Mali, the medical monitor will participate in the safety data review prior to administration of further vaccinations.

## 11. STATISTICAL CONSIDERATIONS

### DESCRIPTION OF STATISTICAL METHODS

This study, like other Phase 1 studies, is basically exploratory rather than confirmatory; its purpose is to estimate AE rates and patterns of immune responses rather than to test formal statistical hypotheses. Estimates will be presented with their 95% confidence intervals.

Descriptive approaches will be used to meet the protocol objectives as stated in **Section 2** of this protocol, as well as formal statistical tests as outlined below. Results will be presented in tabular format, as well as graphically where appropriate.

#### 11.1.1 Primary Objective

The primary objective of this study is to assess safety and reactogenicity of BSAM-2/Alhydrogel®+CPG 7909 in malaria-naïve US adults and semi-immune Malian adults.

- a. The frequency of systemic and local AEs will be summarized.
- b. A line listing of each clinical and laboratory AE classified as local, solicited, or other will be displayed in tables stratified by vaccine allocation and study site.
- c. AEs will be summarized by severity and relationship to vaccine.
- d. The proportion of subjects with at least 1 adverse event will be compared by vaccine and/or dose group within each study site, and tests performed to assess whether these groups differ with respect to these proportions. To see if there is a difference in adverse events between the initial vaccination and the subsequent vaccinations, a sign test will be performed, where the response for each subject is the difference between the numbers of adverse events in the 2 weeks following each vaccination.
- e. SAEs occurring within the study period will be listed by relationship to vaccine.

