## 3. STUDY DESIGN

### OVERALL DESIGN

This is a dose escalating multi-site Phase 1 clinical trial of the blood stage malaria vaccine candidate BSAM-2/Alhydrogel®+CPG 7909. Dose escalation will occur in the first part of the study, conducted in malaria-naïve adults at the Johns Hopkins Center for Immunization Research (CIR), in Washington, DC. Fifteen (15) participants will receive 40 µg BSAM-2/Alhydrogel® + 500 µg CPG 7909 (saline), with a group of 5 vaccinated first, followed approximately 2 weeks later by a group of 10. Providing halting rules are not met, an additional 15 participants will receive 160 µg BSAM-2/Alhydrogel® + 500 µg CPG 7909 (saline), also on a similar staggered schedule. All participants will receive 3 doses of vaccine administered IM, with the first 2 doses approximately 2 months apart and the third dose 6 months after the first. After the Safety Monitoring Committee reviews the safety data (through Study Day 63) of the last group to be vaccinated in the US, the second part of the study will be conducted in semi-immune adults in Bancoumana, Mali. This part of the study will be single-blinded and will include a comparator group. The comparator group in Mali will allow for better interpretation of antibody response in a population which has pre-existing immunity, particularly antibodies to the vaccine antigens, and which may experience malaria infection during the vaccination period, which would also affect antibody levels. Use of a comparator vaccine and blinding will also allow for more objective assessment of adverse events in this population, which has a higher rate of febrile illness and other clinical events that could be perceived as related to vaccination. Thirty (30) participants in Mali will be randomized 1:1 to receive the highest safe dose of BSAM-2/Alhydrogel®+CPG 7909, as determined at the SMC review, or the comparator vaccine (Euvax B/ Hepatitis B Vaccine, Recombinant), on a staggered schedule as in the US. The study vaccination schedule is outlined in **Table 2** below.

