## STUDY ENDPOINTS

### 3.1.1 Primary Endpoints

The incidence and severity of systemic and local adverse events

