10. Laboratory evidence of hematologic disease (absolute leukocyte count  $<3000/\text{mm}^3$  or  $>11,500/\text{mm}^3$ ; hemoglobin  $<0.9$  times the lower limit of normal of the testing laboratory, by gender; absolute granulocyte count  $<1300/\text{mm}^3$ ; absolute lymphocyte count  $<1000/\text{mm}^3$ ; or platelet count  $<110,000/\text{mm}^3$ ).
11. Other condition that, in the opinion of the investigator, would jeopardize the safety or rights of a volunteer participating in the trial or would render the subject unable to comply with the protocol.
12. Participation in another investigational vaccine or drug trial within 30 days of starting this study, or while this study is ongoing.
13. Volunteer has had medical, occupational, or family problems as a result of alcohol or illicit drug use during the past 12 months.
14. History of a severe allergic reaction or anaphylaxis.
15. Severe asthma. This will be defined as:
  - Asthma that is unstable or required emergent care, urgent care, hospitalization or intubation during the past 2 years, or that requires the use of oral or parenteral corticosteroids
  - Clinically significant reactive airway disease that does not respond to bronchodilators
16. Positive hepatitis B surface antigen (HBsAg). Hepatitis C antibody by rapid diagnostic test.
17. Known immunodeficiency syndrome.
18. Use of systemic corticosteroids (excluding topical or nasal) or immunosuppressive drugs within 30 days of starting this study.
19. Receipt of a live vaccine within past 4 weeks or a non-live vaccine within past 2 weeks prior to entry into the study.
20. History of a surgical splenectomy.
21. Receipt of blood products within the past 6 months.
22. Previous receipt of an investigational malaria vaccine.
23. History of use of chloroquine or related compounds (hydroxychloroquine, amodiaquine, or primaquine) within 8 weeks of study entry.

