#### **SAMPLE SIZE AND POWER CALCULATIONS**

The study is powered to provide sufficient safety data before proceeding step-wise (first dose ranging in the US, and then to Malian adults) towards the target population (young children in an endemic area). A sample size of 12 in each group gives a probability of 0.80 for detecting 1 or more adverse events that occur with a probability of 0.125 per subject. We have included 15 per dose group in case of withdrawals or loss to follow-up.

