Other clinical studies of CPG 7909 used as an adjuvant have shown a moderately increased incidence of mild to moderate local and systemic AEs after vaccination (injection site pain, myalgia, fatigue). Transient lymphopenia, neutropenia, and thrombocytopenia have been seen among patients treated with CPG 7909. These AEs will be monitored and recorded as is standard practice. A Phase 3 clinical study of CPG 7909 in patients with advanced nonsquamous cell lung cancer showed a possible increase in sepsis and thrombocytopenia with bleeding events in subjects receiving CPG 7909. No events such as this have been seen in the studies using CPG

7909 as a vaccine adjuvant described in **Section 1.6**. Subjects with fever are excluded from vaccination and hematologic parameters including platelet counts will be monitored.

With the exception of the Phase 1 study of AMA1-C1/Alhydrogel®+CPG 7909 in Malian adults described in **Section 1.6.3**, CPG 7909 has not been administered to humans in malaria-endemic areas, or in populations with a high burden of infectious disease. It is possible that the safety profile and immunologic response to CPG 7909 may be different in these populations.

Animal studies have found serious, unexpected fetal and maternal problems when CPG 7909 was given to pregnant rats and rabbits. These studies used a dose of CPG 7909 more than 100 times higher than the dose used in this study. These problems included decreased maternal and fetal weight gain as well as a variety of malformations of the fetal skeleton and organs. For this reason, women who are pregnant or who may become pregnant will not be enrolled in the study. Women who participate in the study must use a reliable method of birth control before the start of the study and for at least 3 months after receiving the final vaccination. Pregnancy testing will be completed on female subjects multiple times during the trial. Any female participant interested in contraceptive methods will be referred to the local health center family planning services for evaluation and institution of an appropriate contraceptive method.

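### The primary safety analysis uses blood counts only as graded adverse events, so the randomised Mali comparison would probably miss a small or moderate effect that the collected values could estimate

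*Protocol*

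**What the plan says.** The primary endpoint is "The incidence and severity of systemic and local adverse events". Section 11.1.1 lists five analyses, items a to e: event frequencies, a line listing ("A line listing of each clinical and laboratory AE classified as local, solicited, or other will be displayed in tables"), summaries by severity and relationship, a between-group test of the proportion with at least one adverse event plus a within-subject sign test on event counts, and a list of serious events. None of them summarises or compares a laboratory value as a measurement.

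The data for doing so are planned. In Mali, a complete blood count is taken on Day 0 and on Days 3, 7 and 14 after each dose, and again on the day of the second and third doses (Section 6, Clinical Monitoring and Evaluation; Appendix B). The design is randomised: "Thirty (30) participants in Mali will be randomized 1:1 to receive the highest safe dose" or the hepatitis B comparator, with those who assess adverse events blinded.

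A haematological effect is foreseen. The risk section states: "Transient lymphopenia, neutropenia, and thrombocytopenia have been seen among patients treated with CPG 7909". The account of experience with BSAM-2 to date reports mild or moderate neutropenia, and the Halting Rules treat short-lived Grade 2 neutropenia as expected.

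**The concern.** A grade discards most of the information in a count and takes no account of the subject's own starting value. The Mali limits show this in both directions.

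- **Grade without change.** The Mali exclusion criterion that begins "Laboratory evidence of hematologic disease (absolute leukocyte count" admits WBC from 3000/mm³ and granulocytes from 1300/mm³. In Appendix D (Mali), Grade 1 covers WBC below 3500 down to 2500 and neutrophils 1000 to 1500. If the granulocyte limit and the neutrophil grade are read as the same count, a volunteer at 1400 is within Grade 1 on Day 0.
- **Change without grade.** Platelets are graded only below 100,000/mm³, so a fall from 220,000 to 100,000 carries no grade. Male haemoglobin is graded only from 9.5 g/dL down. Lymphocytes have no row in Appendix D, although lymphopenia is a named adjuvant effect.

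The Mali comparator is there partly to make safety assessment more objective, and it is the trial's only randomised contrast of adjuvanted vaccine with a control. Antibody, a secondary endpoint, is compared as change from Day 0 (Section 11.1.2). The expected adjuvant effect on blood counts gets no such analysis.

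**Working it through.** **1. The protocol's own figure.** Sample Size and Power Calculations states: "A sample size of 12 in each group gives a probability of 0.80 for detecting 1 or more adverse events", for "adverse events that occur with a probability of 0.125 per subject". Check: 1 − (1 − 0.125)^12 = 0.799, which agrees with 0.80. At 15 per group it is 1 − 0.875^15 = 0.865. This is the chance of seeing at least one event within one group. It says nothing about a difference between groups.

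**2. Inputs for the comparison.** From the protocol: 15 v 15, and the 12.5% rate, borrowed here as the share of BSAM-2 recipients with a graded value. Assumed, because the protocol gives no figures: comparator share p0 of 1%, 2.5% or 5%; two-sided 0.05; normally distributed values with a common SD and a pure shift; correlation of 0.5 with Day 0.

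**3. Graded comparison.** Fisher's exact test at 15 v 15 needs at least 5 v 0, 7 v 1 or 9 v 2 subjects for significance. Power is the sum of the binomial probabilities over all significant tables.

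**4. Measured values behind the same cut.** The shift in SD units is d = z(1 − p0) − z(1 − p1), with power from the noncentral t. With baseline adjustment, d is divided by √(1 − 0.5²) = 0.866.

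| Graded, BSAM-2 v comparator | Fisher | d | t-test | Baseline-adjusted |
|---|---|---|---|---|
| 12.5% v 1% | 2.7% | 1.18 | 88% | 95% |
| 12.5% v 2.5% | 2.2% | 0.81 | 57% | 70% |
| 12.5% v 5% | 1.5% | 0.49 | 26% | 33% |
| 25% v 1% to 5% | 28% to 17% | 1.65 to 0.97 | 99% to 73% | above 99% to 84% |
| 40% v 1% to 5% | 72% to 52% | 2.07 to 1.39 | above 99% to 96% | above 99% to 99% |

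The continuous test has its own limit. At 15 v 15, 80% power needs a shift of 1.06 SD, and at 12 v 12 it needs 1.20 SD.

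**5. Item d as written (any adverse event).** Background events hide a laboratory effect: 95% v 80% gives 8% power, and 100% v 90% gives 1%.

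**6. Second check by simulation.** Entry-truncated Mali counts were simulated, 4,000 trials per setting, comparing a Wilcoxon test on change from Day 0 with Fisher on Grade 1 or worse. Assumptions: neutrophil median 2500 or 3500, CV 35%; platelet median 220,000, CV 25%; WBC median 5500, CV 25%; male haemoglobin mean 14, SD 1.2 g/dL; correlation 0.5 to 0.7.

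| Shift | Wilcoxon | Fisher |
|---|---|---|
| Neutrophils −20% | 39–58% | 0–6% |
| Neutrophils −40% | 97–100% | 7–69% |
| Platelets −20% | 63–85% | 0% |
| WBC −20% | 62–85% | 6–7% |
| WBC −40% | 100% | 92–94% |
| Male haemoglobin −1.0 g/dL | 57–79% | 0% |

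**7. Precision of an estimate.** The 95% half-width at 15 v 15 is t(0.975, 28) × √(2/15) = 2.048 × 0.365 = 0.75 SD. Adjustment with a correlation of 0.5 reduces it to about 0.65 SD.

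**The case against.** The strongest reply is that change-from-baseline laboratory tables usually belong in a SAP, which is not at hand, and that Section 11.1 declares an estimation purpose and promises descriptive methods with intervals beyond the listed tests. That stands as far as it goes: the absence is not in itself an error. But Section 11.1.1 does set out how laboratory results enter the primary analysis and does choose a between-group test. Neither choice suits the effect the protocol foresees.

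Four further objections limit the point.

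- **No such test is planned.** The protocol plans no Fisher test on a single analyte and claims no power for the Mali contrast. A reader might infer that a power claim is wrong. It is not: the stated 0.80 reproduces.
- **The sizes are assumed.** The 0.125 is a generic event rate, and no SD or expected shift is given. If only a few recipients fell sharply, the advantage of the measured values would shrink.
- **False Grade 1 events need not follow.** A reader might infer that the entry overlap will fill both arms with spurious events. Section 9 defines an adverse event as a change, so a stable low value should not count. The protocol does not say how the tables apply this.
- **A blanket comparison would be excessive.** In Mali, four counts and creatinine at 11 later draws and ALT at 8 make 4 × 11 + 11 + 8 = 63 comparisons, with about 63 × 0.05 ≈ 3 false signals expected. The US dose groups share one nominal CPG 7909 dose and are filled in screening order, so they cannot show the adjuvant effect.

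**Conclusion.** The point holds for small and moderate effects. As Section 11.1.1 stands, such an effect on blood counts in the randomised Mali comparison would probably be missed: 1.5% to 2.7% power for graded proportions at 12.5% v 1% to 5%, against 26% to 88% for the measured values and 33% to 95% with baseline adjustment. These figures rest on the normal-shift model, the assumed comparator shares, a correlation of 0.5 and 15 per arm.

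The documents do not support saying that grades have almost no power in general. At 40% graded, Fisher reaches 52% to 72%, and a 40% fall in WBC is nearly always found either way in the simulation. Nor would measured values detect everything: at about half an SD, their unadjusted power is only 26%. The finding is an inefficient choice of analysis with a cheap remedy. It does not show that the safety plan is invalid.

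**What to change.** Add to Section 11.1.1, as a supportive analysis: *For neutrophils (or granulocytes), WBC, platelets and haemoglobin, the difference between the Mali arms on Days 3 and 7 after each dose will be estimated, adjusted for the Day 0 value, on the log scale where skewed, with 95% confidence intervals and no claim of significance. ALT, creatinine and the US dose groups will be summarised descriptively.*

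For the graded tables, add: *A laboratory adverse event is counted only when its grade exceeds the subject's Day 0 grade.* This applies the existing definition of an adverse event as a change. It is needed because the Mali entry limits for WBC (3000) and granulocytes (1300) fall inside Grade 1.

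If a SAP already contains these analyses, a reference to it in Section 11.1.1 is enough.

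The cost is analysis and table wording, with no new samples, visits or subjects. It adds 4 counts × 2 draws × 3 doses = 24 exploratory estimates, to be read as estimates only. Clinical grading and the Halting Rules stay as they are.
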